| STATISTICAL METHODS               | Demographic characteristics will be reported as measures of central tendency for continuous outcomes and frequency distribution and percentages for binary/categorical data. Consequently, demographic data will be explored for differences at baseline by comparing and testing means. After the termination of the study, the primary and secondary outcomes will be evaluated for normality by the Kolmogorov-Simonov test and visual inspection of histograms. For the primary ordinal outcome, the impact of the intervention program between baseline and follow up of the 2 groups (intervention and comparison group) will be assessed by using linear mixed models for repeated measurements. The same statistical model will be used to evaluate secondary outcomes. |

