## 2.2 Secondary Outcomes

Other measurements include the anthropometry (weight, height, BMI, and waist circumference) as well as the clinical indicators of systolic blood pressure (SBP), diastolic blood pressure (DBP), and glycemic levels (this measurement will provide information on the absence or presence of pre-diabetes, T2DM, and GDM). Moreover, micronutrient adequacy will be evaluated by a dichotomous indicator of the minimum dietary diversity for women developed by the Food and Agriculture Organization of the United Nations (FAO). Also, physical activity frequency, duration, and type of physical activity will be assessed by using the International Physical Activity Questionnaire (IPAQ)-Short version.

To determine the possibility of complementing the intervention program with community based activities, close-ended Likert scale questionnaires with an agreement scale will be performed. Also, focus groups per healthcare center will be carried to understand the acceptability of community support and intervention perception.

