## Dietary evaluation

### **Diet diversity**

The minimum dietary diversity for women (MDD-W) developed by the Food and Agriculture Organization of the United Nations (FAO) is a dichotomous population-level indicator of whether participants have consumed at least five out of ten defined food groups the previous day. The MDD-W is used as a proxy to describe one important dimension of women's diet quality (micronutrient adequacy) in national and subnational assessments.

The general ten groups are presented below (list of foods contained by each group is presented in section 2 of guideline) :

1. Grains, white roots and tubers, and plantains
2. Pulses (beans, peas, and lentils)
3. Nuts and seeds
4. Dairy
5. Meat, poultry, and fish
6. Eggs
7. Dark green leafy vegetables
8. Other vitamin A-rich fruits and vegetables
9. Other vegetables
10. Other fruits

The threshold of this tool is: > 5 groups of food groups consumed indicates better micronutrient adequacy. The interpretation compromises that groups of women of reproductive age where a higher proportion consume food items from at least five of the ten food groups are likely to have higher micronutrient adequacy than other groups that have a lower proportion of women achieving the threshold of food items from at least five food groups. In other words, women of reproductive age who consume food items from five or more of the ten groups are also highly likely to consume at least one animal-source food and either pulses or nuts/seeds and food items from two or more of the fruit/vegetable food group. The MDD-W would be assessed using a questionnaire model (**Annex 7**) and following the guidelines by the FAO. This questionnaire will be conducted and filled in by the health professional.

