### 8.2 Variables of interest

After the termination of the study, the primary and secondary outcomes will be evaluated for normality by the Kolmogorov-Simonov test and visual inspection of histograms. In case of non-normally distributed outcomes, log transformation and non-parametric tests will be considered.

The primary outcome (healthy lifestyle questionnaire score) will be a variable with ordinal values ranging between 14-65 points. The secondary outcomes of anthropometrics (weight [kg], height [m], BMI [kg/m^2], waist circumference [cm]), clinical indicators (glycemia [mg/dL] and blood pressure [mmHg]), and total MET-min/week and kcal/week collected by the physical activity questionnaire will be variables with continuous values. Only the outcome of diet diversity will be provided as an ordinal variables ranging from 0-10.

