#### **8.3.4 Secondary and tertiary analysis**

For secondary ordinal and continuous outcomes (anthropometric, clinical, questionnaires, etc.), exploratory analysis using the same method of linear mixed models for repeated measurements.

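### Diet diversity is defined as a yes/no threshold indicator but planned for analysis as a 0-10 count, so the documents contain no between-arm comparison of the proportion reaching the threshold

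*Combined protocol and SAP*

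**What the plan says.** **Definition.** Section 2.2 (Secondary Outcomes) states that "micronutrient adequacy will be evaluated by a dichotomous indicator of the minimum dietary diversity for women". Section 5.3, under Diet diversity, says that the MDD-W "is a dichotomous population-level indicator of whether participants have consumed at least five out of ten defined food groups the previous day". Its interpretation text compares groups of women by proportions: a group with a larger share at the threshold is set against groups "that have a lower proportion of women achieving the threshold of food items from at least five food groups".

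**Cut-off.** The same part of section 5.3 also says: "The threshold of this tool is: > 5 groups of food groups consumed indicates better micronutrient adequacy". That is a strict inequality, whereas the definition and interpretation sentences use five or more.

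**Analysis variable.** Section 8.2 says: "Only the outcome of diet diversity will be provided as an ordinal variables ranging from 0-10". It lists no binary version.

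**Model.** Section 8.3.4 reads: "For secondary ordinal and continuous outcomes (anthropometric, clinical, questionnaires, etc.), exploratory analysis using the same method of linear mixed models for repeated measurements". The synopsis agrees: "The same statistical model will be used to evaluate secondary outcomes". Section 8.3.6 repeats that primary and secondary outcomes go to a linear mixed model. The only alternatives offered, in section 8.2, are a log transform or non-parametric tests if an outcome is not normally distributed.

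**Six-monthly summaries.** Sections 8.3.6 and 9 list percentages for lifestyle and dietary improvement, physical activity, BMI, pregnancy weight gain, glycemia and blood pressure. MDD-W attainment is not named, and no comparison between arms is described.

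**The concern.** The variable in section 8.2 is not the outcome in sections 2.2 and 5.3. Women with 2, 4 and 7 food groups enter the planned model as 2, 4 and 7. On the defined outcome they are no, no and yes.

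Section 5.3 attaches the micronutrient-adequacy reading to the share of women at the threshold, not to the mean number of groups. If section 8 is followed as written, the trial could draw a conclusion about micronutrient adequacy from a statistic that section 5.3 does not tie to it. With two forms of the outcome in one document, the choice of which to report also stays open after the data are seen. It is unclear, too, which form counts as the outcome when section 8.3.6 divides 0.05 by the number of primary and secondary outcomes.

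**Working it through.** The documents give no expected mean, proportion, effect or power for diet diversity, so there is no stated figure to reproduce. The main check is textual. The arithmetic only illustrates how far the two statistics can differ.

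**1. Passages side by side**

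| Place | Form of the outcome | Between-arm quantity |
|---|---|---|
| Section 2.2 | Dichotomous | Not stated |
| Section 5.3 | Dichotomous | Proportion at the threshold |
| Section 8.2 | Ordinal, 0-10 | Not stated |
| Section 8.3.4 | Ordinal or continuous | Linear mixed model, hence mean count |
| Synopsis; 8.3.6 | Not specific to diet diversity | Linear mixed model |

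Section 8.3.4 does not name diet diversity. Section 8.2 makes it the only secondary outcome described as ordinal, so it falls under that sentence. No place gives a binary-outcome model or a comparison of proportions.

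**2. Illustration**

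Assumption, not from the documents: the count X is Binomial(10, 0.3), mean 3, with P(X = k) = C(10,k) × 0.3^k × 0.7^(10−k).

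- P(X ≤ 3) = 0.028 + 0.121 + 0.233 + 0.267 = 0.650 (unrounded terms sum to 0.6496)
- P(X = 4) = 210 × 0.0081 × 0.1176 = 0.200
- P(X ≥ 5) = 1 − 0.650 − 0.200 = 0.150

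If a share g of all women each gain one group, the mean rises by g. The proportion at five or more rises by the share of all women who are at exactly four and gain.

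- *Gains only among women at three or fewer, g = 0.5.* This is feasible because 0.5 < 0.650. Nobody passes four. Mean +0.5, proportion +0 points.
- *Gains in a random half of women, g = 0.5.* The proportion rises by 0.5 × 0.200 = 0.100. Mean +0.5, proportion +10 points.
- *Every woman at four gains and nobody else does, g = 0.200.* Mean +0.2, proportion +20 points.

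**3. How far this generalises**

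The first case depends on the starting mean. With one-group gains, women at three or fewer can supply a mean rise of at most P(X ≤ 3), which is 0.38 at mean 4 and 0.17 at mean 5. A rise of 0.5 therefore cannot come from that source at those means.

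If instead the whole binomial distribution shifts up by 0.5, for control means from 2.5 to 6.0, the proportion at five or more always rises, by 7.1 to 12.9 points.

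**4. Cut-off**

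For a binomial mean moving from 4.0 to 4.5, the share with five or more goes from 36.7% to 49.6%, and the share with more than five from 16.6% to 26.2%. The two cut-offs in section 5.3 give materially different indicators.

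**The case against.** - **A later SAP may supply the analysis.** Section 8 says that a binding plan will be finalized before database lock or any other analysis. This stands as a limit on the claim. A reader might infer that the trial will never compare the arms on the defined outcome. The documents do not support that; they show only that no such comparison is in this text.
- **The count is legitimate.** This stands. A 0-10 count uses more of the information than a dichotomy does, and section 2.2 could be amended to name it as the outcome. The fault is that the two sections disagree, not that a count is invalid.
- **The blanket wording in 8.3.6 could cover a 0/1 variable in a linear model.** It could if section 8.2 supplied a 0/1 variable, but 8.2 supplies 0-10 and 8.3.4 names only ordinal and continuous outcomes. The non-parametric fallback does not yield the proportion either.
- **In practice the two statistics will usually agree in direction.** Under a plain shift of the distribution they do, as shown above. The 0-point and 20-point cases are constructed extremes. A reader might infer that the mean count will probably mislead; the documents give no food-group distribution that could support that.
- **No data are lost.** This is correct. The Annex 7 questionnaire records the food categories, so the indicator can be derived at any time.

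**Conclusion.** The inconsistency is real. Sections 2.2 and 5.3 define a dichotomous indicator, section 8 analyses a 0-10 variable with a linear mixed model, and no analysis in the combined document compares the arms on the proportion reaching the threshold. A mean difference does not determine the difference in that proportion. At an assumed binomial mean of 3, a rise of 0.5 groups can go with 0 or about 10 points, and a rise of 0.2 with as much as 20 points. These sizes rest wholly on the binomial assumption and on who is assumed to gain.

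The weight is moderate. This is one secondary outcome, its analysis is labelled exploratory, and the hypotheses, sample size and power concern only the lifestyle score. Settling the cut-off alone would not close the gap, because there would still be no comparison of proportions.

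**What to change.** 1. In section 5.3, reconcile the strict cut-off with the five-or-more wording. The definition and interpretation sentences both use five or more.
2. In section 8.2, derive the binary MDD-W indicator for each woman at each visit, alongside the 0-10 count.
3. In section 8.3.4, add a between-arm comparison of the proportion reaching the threshold that allows for repeated measures and for the six centres. Either a binary mixed model with a small-sample method or an analysis of centre-level proportions would serve.
4. Keep the count as a further analysis, and state which of the two enters the Bonferroni divisor in section 8.3.6.

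If the sponsor prefers the count as the outcome, section 2.2 should say so, and the micronutrient-adequacy reading in section 5.3 should not be attached to it without justification.

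The cost is some wording and one extra model on data already being collected, and it can be settled in the SAP announced in section 8. The downside is that the binary indicator is less precise than the count, which is why the count should stay.

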### 8.3 Statistical methods

#### 8.3.1 Analysis populations

The analyses will be conducted based on the intention-to-treat principle. A probability of <0.05 will be considered statistically significant for all tests. All analyses will be conducted using STATA (Release 16/SE. College Station, TX: StataCorp LP) by ITM's staff.

#### 8.3.2 Baseline characteristics

After the initiation of the study, demographic characteristics will be reported as measures of central tendency (mean and SD or median and interquartile range) for continuous outcomes and frequency distribution and percentages for binary/categorical data. Demographic data will be explored for differences at baseline by comparing and testing means of all demographic and baseline data.

#### 8.3.3 Primary analysis

After the termination of the study, the primary and secondary outcomes will be evaluated for normality by the Kolmogorov-Simonov test and visual inspection of histograms. For the primary ordinal outcome (Healthy lifestyle Questionnaire Score), the impact of the intervention program

between baseline and follow up of the 2 groups (intervention and comparison group) will be assessed by using random effect (clusters) linear mixed models for repeated measurements.

#### **8.3.4 Secondary and tertiary analysis**

For secondary ordinal and continuous outcomes (anthropometric, clinical, questionnaires, etc.), exploratory analysis using the same method of linear mixed models for repeated measurements.

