| FOLLOW-UP                         | Participants will be followed up for 24 months and measurements will be assessed every 6-months period (total of 5-time points: baseline + 4 follow up visits).                                                                                                                                                                                                                                                                                                                                                                                                                                                                                                                                                                                                                 |
| ANALYTICAL METHODS                | Not applicable.                                                                                                                                                                                                                                                                                                                                                                                                                                                                                                                                                                                                                                                                                                                                                                 |
| SAFETY                            | This study imposes a low risk for the participants as the intervention program comprises a lifestyle modification through education and motivational strategies and the measurements to be taken are non-invasive, with the exception of blood glucose assess by blood sampling using a finger prick. For this measurement, guidelines with all the necessary steps and equipment will be followed.                                                                                                                                                                                                                                                                                                                                                                             |

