### 4.2 Inclusion and exclusion criteria

To be eligible, study participants must meet the following criterium:

- Non-pregnant or (first trimester) pregnant women of reproductive age (18-49 years old), without a previous diagnosis of type 1 diabetes or T2DM (confirmed by a random glucose test, which is a random blood test to check the glucose levels at random and no fasting condition is required. This test will be carried out by pricking the fingertip with a lancet and glucometer to all women during the recruitment).

Potential participants meeting any of the following criteria will not be enrolled in the study:

- Pregnant women with active GDM
- Adult males, and children and adolescents <18 years old of both sexes
- Pre-existent severe chronic conditions (e.g. chronic liver or kidney disease, chronic obstructive pulmonary disease (COPD))
- Living outside of the surrounding catchment areas of the 6 healthcare centers.
- Women internationally displaced, without a permanent home or identified physical address. This to decrease the possibility of drop-outs.
- Women planning to move elsewhere in the following 2 years
- Women that do not provide a written IC.

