| Physical activity                                            |                               |                                         |           |          |           |           |           |
| Physical activity questionnaire**                            | IPAQ-short version            | Health professional                     | X         | X        | X         | X         | X         |
| Acceptability of community support (only intervention group) |                               |                                         |           |          |           |           |           |
| Agreement scale questionnaire                                |                               | Health professional                     |           | X        | X         |           |           |
| Intervention assessment (only intervention group)            |                               |                                         |           |          |           |           |           |
| Focus groups                                                 |                               | Peer educators and health professionals |           | X        | X         | X         | X         |

Abbreviations: Body mass index (BMI); Type 2 diabetes mellitus (T2DM); Gestational diabetes (GDM) ; Minimum dietary diversity for women (MDD-W) In addition to these measurements, the ANC reports of pregnant women will be requested to the healthcare centers.

\*Primary outcome. \*\*Secondary outcome. †OMRON: Digital automatic blood pressure monitor. ~ 24-hour dietary recall will also be assessed randomly within the 6 month period, this will be performed by the health professional and by telephone. For pregnant women the weight will be compared to the recommended gain weight based on pre-pregnancy BMI, as follows: Underweight (BMI < 18.5): 13-18 kg; Normal weight (BMI 18.5 – 24.9): 11-16 kg; Overweight (25 - 29.9): 7-11 kg; Obese (BMI > 30): 5-9 kg.

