#### **8.3.5 Subgroup analyses**

To explore differences in the evolution between pregnant and non-pregnant women, subgroup analysis for the primary and secondary outcomes will be performed. Other potential subgroup analysis will compromise healthy and unhealthy subgroups based on BMI, glycemia and blood pressure at baseline to assess their evolution and identify the subgroups with larger and smaller effects on the primary and some secondary outcomes.

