#### **8.3.6 Multiplicity and Missing Data**

Bonferroni's p-value correction for multiple comparisons will be considered. This will be performed by dividing the total p-value (0.05) by the final number of outcomes used in the final analyses (primary + secondary outcomes). Moreover, as mentioned the analysis will be performed under the ITT principle. To avoid and/or decrease missing data, particularly in the questionnaires, health professionals will be asked to revise the questionnaires for completeness right after the participants have filled them up. In the case of missing answers, participants will be asked to provide an answer to the questions. Nonetheless, the primary and secondary outcomes will be assessed by a linear mixed model, which is a model that can handle missing values by using maximum likelihood estimations.

Interim analyses will be performed for the primary and secondary parameters will be assessed after the completion of each set of measurements (~ 6 months) by quantifying the % of women improving dietary habits and physical activity levels and categorizing into different levels of improvement, % of women with a BMI <25 kg/m^2, % of pregnant women gaining the correct amount of weight based on their pre-pregnancy BMI, % of women with normal glycemia levels, and % of women with normal blood pressure. Also, evaluation of intervention program indicators will be performed though summarizing the % of trained peer educator and health professionals, % of optimal data available for key indicators and the % of patients who have withdrawn the IC.

Moreover, to determine whether it is feasible and acceptable to complement the intervention program with community based-strategies, the Likert scale will be summarized by frequency distribution and percentages, this will be carried out during the first year of intervention program.

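### The weight, BMI and waist models pool pregnant, post-partum and non-pregnant visits without a pregnancy term, and gestational gain at 6-monthly visits is scored against whole-pregnancy ranges

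*Combined protocol and SAP*

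**What the plan says.** - **Population (4.2).** One cohort: "Non-pregnant or (first trimester) pregnant women of reproductive age (18-49 years old").
- **Schedule (Synopsis).** "measurements will be assessed every 6-months period (total of 5-time points: baseline + 4 follow up visits"). Table 1 places weight, BMI and waist at all five.
- **Model.** The primary score "will be assessed by using random effect (clusters) linear mixed models for repeated measurements" (8.3.3). Section 8.3.4 carries this over: "For secondary ordinal and continuous outcomes (anthropometric, clinical, questionnaires, etc.), exploratory analysis using the same method of linear mixed models". Neither section names a term for pregnancy, gestational week or time since delivery.
- **Gestational gain.** The Table 1 footnote says: "For pregnant women the weight will be compared to the recommended gain weight based on pre-pregnancy BMI", with one range per BMI class (13–18, 11–16, 7–11 and 5–9 kg). Section 8.3.6 summarises, after each set of measurements, the percentage "of pregnant women gaining the correct amount of weight based on their pre-pregnancy BMI". Section 9 repeats this among the data-quality checks.
- **Partial provisions.** Section 8.3.5 plans a subgroup analysis of primary and secondary outcomes, "To explore differences in the evolution between pregnant and non-pregnant women". A note under Table 1 says antenatal care (ANC) reports will be requested, but states no analytic use for them.
- **Not scheduled.** Neither Table 1 nor the baseline questionnaire in 5.3 lists pregnancy status by visit, gestational week or pre-pregnancy weight.

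**The concern.** A woman enrolled in the first trimester contributes an early-pregnancy weight, then a late-pregnancy weight, then post-partum weights. Others conceive during the 24 months. The planned model treats all of these as one outcome with one error structure. At best that inflates the residual variance. At worst, if one group of centers has more pregnant women or a different timing of pregnancy, the difference appears in the arm contrast for weight, BMI and waist.

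The gain percentage has a different fault, which is present even when the arms are alike: a part-pregnancy weight is held against a full-pregnancy range. Specific objectives 1 and 2 in section 2 concern overweight and obesity, and healthy weight gain in pregnancy, so these are the measurements a reader would turn to.

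**Working it through.** **The plan's own figure.** The only stated power is for the primary score (4.3 and 8.4: 40 per center, 3 centers per arm, difference 6, SD 7, ICC 0.1, one-sided 0.05). Design effect = 1 + 39 × 0.1 = 4.9. Effective n per arm = 120/4.9 = 24.5. SE = 7 × √(2/24.5) = 2.00. Power = Φ(6/2.00 − 1.645) = 0.912, against 91% stated. It reproduces with a normal approximation, and the present point does not touch it. No effect, SD or power is given for weight, BMI or waist.

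**1. The ranges are totals.** Section 1.1 gives 11–20 pounds during pregnancy for obese women. At 0.4536 kg per pound that is 5.0–9.1 kg, which is Table 1's 5–9 kg. The normal-weight 25–35 pounds is 11.3–15.9 kg, which is Table 1's 11–16 kg. (The overweight figure in 1.1 does not match Table 1's 7–11 kg. The two must be reconciled; Table 1 is used below.)

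**2. Where visits fall.** Enrolment is taken as weeks 4–13 (assumed). Month 6 adds 26 weeks, giving weeks 30–39. Month 12 adds 52, so the woman has delivered. Only one follow-up visit falls within the enrolled pregnancy.

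**3. Misclassification by timing.** Assumed path: 0.5–2 kg gained by week 13, then linear to the midpoint of the range at week 40. For normal BMI the midpoint is 13.5 kg.
- Gain at week 30: 0.5 + 13 × 17/27 = 8.7 kg, or 2 + 11.5 × 17/27 = 9.2 kg. At week 39 it is 13.0–13.1 kg.
- Week at which 11 kg is reached: 13 + 27 × 10.5/13 = 34.8, or 13 + 27 × 9/11.5 = 34.1.
- Share of on-track women below 11 kg at month 6, with enrolment uniform over weeks 4–13: (34.8 − 30)/9 = 53%, or (34.1 − 30)/9 = 46%.
- Across the four BMI classes the share is 0–61%, measured from pre-pregnancy weight.
- If the baseline weight stands in for pre-pregnancy weight, it is 62–97% for normal BMI and 31–100% across classes.
- For a pregnancy starting during follow-up and seen at a random week, it is 34.1/40 to 34.8/40 = 85–87% for normal BMI, and 73–89% across classes.

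**4. How common pregnancy is.** Section 4.1 gives 4,200 pregnancies a year in about 107,000 inhabitants. If women aged 18–49 are 18–25% of the population (assumed), the rate is 4,200/26,750 to 4,200/19,260 = 0.157–0.218 per woman-year. Multiplying by 0.75 year gives 12–16% pregnant at any time. 1 − exp(−2 × rate) gives 27–35% with a pregnancy in 24 months.

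**5. Shift in mean weight.** Shift = difference in share × kg gained. A 10-point difference in late pregnancy gives 0.10 × 6 to 0.10 × 12 = 0.6–1.2 kg.

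Chance imbalance in the share pregnant at any stage, with 13% pregnant and ICC 0.01–0.1 (both assumed), is 1.96 × √(2 × 0.13 × 0.87 × (1 + 39 × ICC)/120) = ±10 to ±19 points. At 9 kg gained, typical of late pregnancy, that is ±0.9 to ±1.7 kg. At the average gain over a normal-BMI pregnancy (4.8–5.6 kg on the path above) it is about ±0.5 to ±1.1 kg.

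**The case against.** The strongest reply is that both arms share one schedule, so pregnancy timing is noise unless the arms differ. That stands. A reader might infer that these outcomes measure pregnancy timing rather than the programme; the documents do not support that. They do leave imbalance possible. Section 4.4 balances two hand-made groups of three centers on population size and urban or rural area only, and 4.1 recruits partly through antenatal and post-natal care.

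The 10-point scenario is also demanding. If late pregnancy lasts a quarter of a year, the rates above put 3.9–5.5% of women there at a random visit. A 10-point gap is plausible mainly at month 6, among women enrolled pregnant, and their number is not stated.

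A reader might also infer that most women weighed before term would be scored as under-gaining. That does not hold generally. It is about half for normal-BMI women enrolled pregnant and as low as 0% for obese women on one path, when gain is counted from pre-pregnancy weight. It does hold for pregnancies starting during follow-up.

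The subgroup in 8.3.5 and the ANC reports are real provisions but do not close the gap. The plan does not say whether subgroup status is fixed at baseline or updated. A baseline-pregnant subgroup would still mix late-pregnancy and post-partum weights.

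Finally, 8.3.4 is labelled exploratory, and the gain percentage is a periodic summary that 8.2 does not list as an outcome. Both are true and limit the weight of the point. Still, 8.3.1 applies the 0.05 threshold to all tests, and no other analysis of gestational gain is stated for objective 2.

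**Conclusion.** The point holds, at moderate weight and for exploratory outcomes only.

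- **Models.** Omitting pregnancy status adds variance to weight, BMI and waist. It biases the contrast only if pregnancy mix or timing differs by arm, by about 0.6–1.2 kg per 10 points of late-pregnancy imbalance (6–12 kg gained, assumed). With no SD for weight in the documents, this cannot be turned into power or type I error.
- **Gain percentage.** As written, the rule misclassifies a substantial share of on-track women through visit timing, whether or not the arms differ. Any arm comparison of it would also depend on the gestational-week mix. The sizes rest on the assumed gain path and enrolment weeks.

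It would be wrong to infer any threat to the healthy lifestyle score.

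**What to change.** 1. Record pregnancy status and gestational or post-partum week at every visit.
2. In the SAP, which section 8 says is finalised before database lock, add time-varying status (not pregnant, pregnant, post-partum) to the weight, BMI and waist models. Exclude pregnant and post-partum visits only as a sensitivity analysis. Exclusion as the main analysis would select on a post-randomisation state, sit uneasily with intention-to-treat, and drop the baseline weight of every woman enrolled pregnant. The status term also conditions on something arising after randomisation, but it keeps all women.
3. Define the 8.3.5 subgroup by pregnancy status at baseline.
4. Assess gestational gain only among pregnancies and relative to gestational week, using the last available antenatal weight and its week. Fix the scaling method in advance, because it matters. At week 32 the 11 kg floor becomes 11 × 32/40 = 8.8 kg if scaled from week 0, or 11 × 20/28 = 7.9 kg if scaled from week 12. A woman heading linearly from week 12 to 12 kg has 12 × 20/28 = 8.6 kg, so she fails the first and passes the second.
5. State which weight stands in for pre-pregnancy weight in women enrolled pregnant.

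**Cost.** Two form fields, SAP wording and abstraction of the ANC reports already requested. Some last antenatal weights will be early, because 4.1 expects only 25% of women to attend four ANC visits; hence the need to record the week. Status and week not captured at the visit may not be recoverable later.
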